#### Eye Movement Desensitization and Reprocessing

A licensed clinical psychologist will conduct the EMDR sessions according to the original protocol developed by Shapiro in 1987 [31]. This is a scientifically grounded, psychotherapeutic approach that represents a specific method within a wider theoretical model called “Adaptive Information Processing (AIP)” [31]. This term refers to the innate capacity of the brain to process life experiences and incentives to achieve an adaptive solution. The AIP model states that the information processing system of the brain can become obstructed as a result of psychological trauma and that specific methods, such as EMDR, are a catalyst for effective information processing that leads to a rapid and adaptive processing of the trauma [32]. Tinnitus can be interpreted as trauma at the level of the auditory regions of the brain. The development of new neural networks where the tinnitus sound is processed as neutral and non-threatening could be generated through EMDR. Eye movements, tactile stimulation (buzzers) and auditory stimuli (headphone) can be used to facilitate the activation of the left and right side of the brain. Within the treatment this is called bilateral stimulation [10, 31–33].

The trauma-network is stimulated through a combination of standardized procedures that include these repetitive eye movements, auditory signals and tactile vibrations. To induce the stimuli, a validated EMDR tool is used to help the clinician. The EyeScan 4000 will be used in this study to guarantee continuity in the visual, auditory and tactile stimuli that are used to stimulate bilateral activation. The original EMDR protocol developed by Shapiro will be followed in order to guarantee validity and test-retest reliability [34] Table 2.

**Table 2 Tab2:** Summary of the intervention based on the standard treatment Eye Movement Desensitization Reprocessing (EMDR) protocol by Shapiro (2001) [13]

Phase Number		
Phase 1	Client history	Negative thoughts, feelings, sensations and experiences associated with the complaints will be identified
Phase 2	Preparation phase	State stability of the client Secure a “stop” sign Installation of the calm/safe place
Phase 3	Assessment phase	Target issue, memory, event, or symptom Target image Negative cognition: NC Positive cognition: PC VoC (Validity of Cognition) Emotions SUDs (Subjective Units of Distress) Location of bodily sensation
Phase 4	Desensitization phase	“*Bring the target image and negative cognition to mind, notice where you are feeling it in your body*” Set of bilateral stimuli (BLS) as fast as the client can tolerate After a set: “*What do you get now?*” “*What are you noticing?*” If client reports new material: “*Go with that*”.
Phase 5	Installation phase	“*Do the words PC still fit, or would another positive statement be more suitable?*” Check VoC: “*Think about the original incident and the words PC. How true do they feel now* (1–7)*?*” “*Bring the target image and positive cognition together in your mind.*” Completion of sets of BLS until no change
Phase 6	Body scan	The client will be asked to mentally scan the entire body and report to the therapist what they can feel
Phase 7	Closure	The therapist will end the session by checking if the client feels calm. Gain of the session and reactions that can appear after the session will be discussed
Phase 8	Reevaluation	The client gives an assessment of the results achieved in the follow-up session

Note: Summary based on the standard protocol of Shapiro, F. (2001) [13]. Eye movement desensitization and reprocessing. Basic principles, protocols and procedures (2nd ed.). New York: Guilford Press

The protocol contains eight phases. The first phase is the Client History in which the focus lies on the tinnitus complaints. In this phase the negative thoughts and experiences will be identified. In the second phase, the Preparation phase, stabilization techniques such as inducing a “safe place” will be addressed. In the Assessment phase the clinician identifies the components of the target being the tinnitus complaints. The negative belief, emotional and physical sensations about the tinnitus will be made concrete. The patient will rate the amount of distress using the 0–10 (0 = neutral to 10 = the worst disturbance imaginable) Subjective Units of Disturbance Scale (SUDS) and the strength of the desired belief by using the Validity of Cognition scale (VOC) with a range of 1–7 (1 = completely false to 7 = completely true).

In the reprocessing phases, consisting of the Desensitization and Installation phase and Body Scan, the bilateral stimulation will be used to activate the traumatic network. During these phases the clinician will monitor how the patient is processing information associated with the tinnitus. In the last phases, the Closure and Reevaluation phases, the patient is brought to equilibrium, and the distress level and positive treatment effects will be evaluated. Every patient who is randomized in the TRT + EMDR group will receive five 60-min sessions of EMDR over five consecutive weeks.

### Side effects

There are no known side effects of TRT, CBT or EMDR. It is possible that some emotions are triggered and temporarily elevated due to the processing of certain experiences.

### Ethics

Written consent will be obtained from every patient. The Ethical Committee of the Antwerp University Hospital approved the study protocol on 17 October 2016 with protocol number EC UZA 16/35/360.

### Assessment measures

Subjective and objective assessment measures will be used to assess the effectivity of both interventions. Self-reported assessment measures and questionnaires provide us with important subjective information. To date, tinnitus research is being challenged to provide objective measures as well. By performing ERP assessment we are able to collect objective data. In Fig. 2 we give an oversight of the enrollment, interventions and assessment for the two bimodal therapies.

**Fig. 2 Fig2:**
[figure not shown]
Standard Protocol Items: Recommendations for Interventional Trials (SPIRIT) guideline schedule of enrollment, interventions and assessments for both intervention groups

### Primary outcome measurement

#### Tinnitus Functional Index (TFI)

The TFI is a self-reported questionnaire, consisting of 25 questions, which assesses the impact of tinnitus on patients’ daily lives [35, 36]. The patient answers each question on a Likert scale ranging from 0 to 10. Questions 1 and 3 are expressed in percentages, and the Likert scale ranges from 0 to 100%. The total score is calculated with the mean of all questions. The answers are converted and the total score is expressed as a number between 0 and 100. In addition to the total score, the score of eight subscales can be determined. The subscales are the following: intrusiveness, reduced sense of control, cognitive interference, sleep disturbance, auditory difficulties attributed to tinnitus, interference with relaxation, reduced quality of life and emotional distress.

A decrease in the score on the TFI in the TRT-CBT treatment group versus a decrease in the TFI score in the TRT- EMDR-treatment group is the primary focus of attention in this study.

### Secondary outcome measurements

#### Visual Analogue Scale (VAS) of loudness

The patient scores the mean and maximum loudness of their tinnitus on a scale of 0 (absence of tinnitus) to 100 (as loud as possible, cannot be any louder).

#### Tinnitus questionnaire (TQ)

The TQ is a 52-item, self-rating scale, which differentiates between dimensions of emotional and cognitive distress, intrusiveness, auditory perceptual difficulties, sleep disturbances and somatic complaints. The patient rates the items on a 3-point scale [37].

#### Hospital Anxiety and Depression Scale (HADS)

The HADS consists of 14 questions that assess anxiety and depression [38, 39]. The patient can choose between four answer options for each question. The score for both components is a summation of the scores of all the questions belonging to the subscale. A result greater than 8 suggests the presence of a depression and/or anxiety disorder.

#### Hyperacusis Questionnaire (HQ)

The HQ is a 14-item questionnaire that surveys a patient’s hypersensitivity to sound [40]. There are four answer options for every question: “no,”, “yes a little,” “yes quite a lot” and “yes a lot” A score of 28 is the cut-off for auditory hypersensitivity.

#### Psychoacoustic measurements

Psychoacoustic characteristics, such as frequency of tinnitus, loudness of tinnitus, and residual inhibition will be determined.

The frequency of tinnitus will be determined by means of frequency matching for which a forced-choice technique is applied. The patient must choose between two presented tones or noises until a tone or noise is found that is similar to the patient’s tinnitus. In case of unilateral tinnitus, the contralateral ear is used as the test ear for frequency matching. In case of bilateral tinnitus, the test ear can be chosen arbitrary. The loudness matching will be performed by comparison of the tinnitus to a pure tone or noise in the ipsilateral ear. Finally, the residual inhibition is the suppression of the patient’s tinnitus, measured by presenting a narrowband noise, 15 dBHL louder compared to the tinnitus loudness, in the ipsilateral ear. This procedure can (partially) mask the tinnitus, which is called a (partial) positive result. When the tinnitus becomes louder, it is called rebound. However, some patients do not notice any change.

#### Audiologic measurements

Impedance measurements will be performed in order to exclude active middle-ear pathology, which is an exclusion criterion of the current study.

In order to categorize our patient group, all subjects will undergo an audiometric hearing test according to current clinical standards (International Organization for Standardization (ISO) 8253–1:2010) with a two-channel Interacoustics AC 40 (Interacoustics A/S, Middelfart, Denmark) in a soundproof audiometric booth. A TDH-39 headphone is used as transducer to measure air conduction thresholds of frequencies ranging from 125 Hz to 16 kHz. Bone conduction thresholds will be determined within a range of 250 Hz to 4 kHz.

In addition, Distortion Product Otoacoustic Emissions (DPOAEs) will be measured at baseline using a pair of two pure-tone frequencies (f1 and f2) closely spaced and presented simultaneously at a level of 65 dB Sound Pressure Level (SPL) for f1 and 55 dB SPL for f2 (frequency ratio f2/f1 = 1.22). The largest and most robust distortion product is 2f1-f2 and can be detected in almost all normal ears.

The last conducted test is the speech-in-noise (SPIN) test. The Leuven Intelligibility Sentence Test (LIST) [41] will be performed. An adaptive procedure is used with the noise at a fixed level of 65 dB SPL. Initially, the speech-to-noise ratio is equal to 0 dB Signal to Noise Ratio (SNR), which implies that the noise and the speech are presented equally loud. Subsequently, the intensity of the speech is varied in steps of 2 dB adaptively in a 1-down (when the keywords in the sentence are repeated correctly), 1-up (when the keywords in the sentence are repeated incorrectly) procedure to determine the 50% correct identification point. This point is called the speech reception threshold (SRT), expressed in dB SNR, and will be determined for each ear. A training list for each ear will be conducted before starting the test.

#### ERP

In this study, the emphasis is on the late auditory evoked potentials, which will be induced by use of a classical oddball paradigm. As such, a standard tone of 1 kHz is repeated with a probability of 80% randomly interrupted by an oddball (or infrequent) tone of 2 kHz with a probability of 20%. This paradigm elicits late auditory evoked potentials comprising of P1-N1-P2 and P300 of which the first complex is mostly generated by bottom-up processes in the brain. The later P300 potential requires more top-down cognitive brain processes and can be seen as an expression of higher cognitive sound processing in tinnitus patients. The hypothesis is that, given the continuous auditory processing of the tinnitus signal, the brain may have less capacity left to align to other incoming stimuli, which may be altered by therapy.

The late auditory potentials will be measured prior to the therapy, after the therapy and 3 months later.

### Statistical methods

Data will be analyzed with SPSS statistical software version 20 (SPSS Inc., Chicago, IL, USA). Descriptive analyses as means and standard deviations (SDs) will be used to describe the characteristics of the participants. Results of both intervention arms will be compared using linear mixed models, accounting for the non-independence of observations within the same individual by including random effect terms into the model. The outcome measurements will be entered as dependent variables. In case this outcome variable shows a non-normal distribution, the data will first be logarithmically transformed. Intervention group (TRT + CBT versus TRT + EMDR) and test moment (T0, T1, T2) are entered as fixed effects. The significance level will be set at *p* < 0.05. The effect of bimodal therapy 1 (TRT + CBT) versus bimodal therapy 2 (TRT + EMDR) will be verified.

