### Sample size calculation

A sample size calculation was carried out to determine the sample size required to obtain a power of 80% with α = 0.05 in a two-sided, two-sample *t* test. Assuming an average difference of 0.7 SD between both treatment groups – simplifying the calculation by considering the change in outcome between the first and the last point – a power of 80% is reached with minimal sample size of 65 patients per treatment group. To cover possible drop out, 166 patients will be randomized between therapy group TRT + CBT and therapy group TRT + EMDR. The CONSORT guidelines will be followed and the enrollment data will be transferred into the flow diagram.

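### The log-transformation rule is triggered by the distribution of the raw outcome and, if it fires, replaces the TFI point difference with a ratio that is undefined at scores of zero

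*Protocol article*

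**What the plan says.** All of this is in the protocol article.

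- **Statistical methods, model and scope:** "Results of both intervention arms will be compared using linear mixed models", with random effects and with group and test moment as fixed effects. "The outcome measurements will be entered as dependent variables", so what follows applies to the primary outcome as well as the secondary ones.
- **Statistical methods, rule:** "In case this outcome variable shows a non-normal distribution, the data will first be logarithmically transformed".
- **Tinnitus Functional Index:** "The answers are converted and the total score is expressed as a number between 0 and 100". The primary focus is "A decrease in the score on the TFI in the TRT-CBT treatment group versus a decrease in the TFI score" in the other arm, which is a difference in points.
- **VAS of loudness:** scored "on a scale of 0 (absence of tinnitus) to 100", so zero is a defined and desirable result.
- **Inclusion criteria:** TFI must be at least 25 and below 90 at entry. Nothing limits it at T1 or T2.
- **Sample size calculation:** "power of 80% with α = 0.05 in a two-sided, two-sample" *t* test, on the change between the first and last time points, with a difference of 0.7 SD. That is an additive scale.

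**The concern.** The rule fixes both a trigger and a remedy, and neither suits the primary analysis.

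**Trigger.** As worded, the check is on the outcome variable. A linear mixed model assumes roughly normal residuals and random effects. The raw TFI can look non-normal when the model is adequate: T0 is cut off at both ends by the entry rule, and the pooled scores mix three visits and two arms.

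**Remedy.** The log has no value at zero. TFI cannot be zero at T0 but can be at T1 and T2, so any loss falls on the patients with the best possible result after treatment. If a constant is added instead, its choice affects the answer, and the stated rule provides none.

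**Effect measure.** On the log scale the arms are compared by a ratio of geometric means. That is not the decrease in TFI score defined as the primary focus, nor the quantity used to size the trial. Which of the two is reported would depend on the shape of the data.

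**Working it through.** **1. Scale of the plan's own figure.** Per arm, n = 2(z₀.₉₇₅ + z₀.₈₀)²σ²/Δ², with (1.960 + 0.842)² = 7.849 and Δ = 0.7.
- σ = √2 (0.7 SD read in units of the single-visit SD, uncorrelated visits): 2 × 7.849 × 2 / 0.49 = 64.1, so 65. The stated 65 per group is reproduced.
- σ = 1 (0.7 SD read in units of the change SD): 2 × 7.849 / 0.49 = 32.04, so 33.

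Either way the planned quantity is a difference in untransformed change. The point below does not depend on which reading was meant.

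**2. Weight of a fall on the log scale.** ln(30/20) = 0.405 and ln(80/70) = 0.134; 0.405/0.134 = 3.0. Both patients improve by 10 points.

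**3. The two scales can rank the arms differently.** Constructed example, two patients per arm:

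| Arm | Scores | Mean change | Geometric mean ratio |
|---|---|---|---|
| A | 80→56, 30→28 | (−24 − 2)/2 = −13.0 | √(0.700 × 0.933) = 0.81 |
| B | 80→72, 30→16 | (−8 − 14)/2 = −11.0 | √(0.900 × 0.533) = 0.69 |

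A is better in points, B on the log scale.

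**4. How often zeros might occur.** The protocol gives no TFI distribution, so these inputs are assumed: T0 mean 50 to 60 and SD 18 to 20 before truncation to 25–<90; mean fall 10 to 20; SD of change 12 to 18; follow-up scores clipped at 0.
- Base case (T0 mean 50, SD 20; fall 20, SD 15): 6.0% zeros; skewness 0.30 raw and −1.76 for log(x+1).
- Over the whole grid: zeros 0.4% to 8.1%; raw skewness about 0 to 0.36; log(x+1) skewness −1.6 to −2.7.

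The transformed scores were more skewed than the raw ones in every cell.

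**5. Raw outcome against residuals.** Illustrative simulation: 65 per arm, T0 and one follow-up, T0 from N(50, 18) truncated as above, mean change −10, −15 or −20, change SD 18, group effect 0 or −9 points. Shapiro–Wilk at p < 0.05 stands in for the unstated check.

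| Distribution checked | Flagged non-normal |
|---|---|
| TFI at T0 | 65–70% of runs |
| TFI pooled over visits and arms | 24–99.9% |
| Within-group change residuals | 5–15% |

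**6. Error rates in the same simulation.**

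| Analysis | Power at −9 points |
|---|---|
| Raw scale | 79% |
| Log, zeros dropped | 46–55% |
| log(x+1) | 61–62% |
| Switch to log (zeros dropped) when pooled TFI is flagged | 46–64% |

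With no group effect, rejection was 4.6% to 5.7% in all variants. The runs with an effect had 6.9 to 15.8 zeros among 130 patients (5% to 12%), so fewer zeros would change the figures for the variants that drop them.

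**The case against.** **The rule is written down in advance.** A reader might infer that the sponsor could choose the scale after seeing the treatment comparison. The document does not support that. Condition and remedy are both pre-specified, the Dissemination protocol section places unblinding at the end of the study, and the check could be made blinded. The simulation shows no excess of false positives. This stands. Blinding would not, however, give a zero score a logarithm or turn a ratio back into a point difference.

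**The wording may be shorthand.** A condensed article may write outcome where residuals are meant, and the diagnostic, the offset and the back-transformation can be left to an analysis plan. Their absence is therefore not held against the protocol, and no formal test is named that could be called wrong. What remains is the stated trigger and the stated remedy.

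**The trigger might not fire.** Raw skewness in the base case is only about 0.3 after treatment and 0.24 at T0, which many analysts would accept by eye. The high flag rates rest on an assumed Shapiro–Wilk rule. This stands: the change of scale is conditional.

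**Zeros may be rare.** A TFI total of 0 needs all 25 items at zero, and clipping simulated negatives does not model that. This also stands, and is why a range is given.

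**Wider reach.** It is tempting to extend the zero problem to HADS, HQ and ERP. The protocol gives no item coding or lower limit for the first two and does not say whether ERP amplitude or latency is analysed. Only TFI and VAS have a documented zero.

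**Conclusion.** The point holds for TFI and VAS. The protocol ties the scale of the primary analysis to the shape of the raw outcome and fixes a remedy that fails at permitted scores and estimates something other than the decrease in TFI score.

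Three parts need no assumption: the log is undefined at zero, a 10-point fall is weighted 3.0 times as heavily from 30 as from 80, and the effect becomes a ratio. The rest is illustrative: how often the rule would fire, the share of zeros (0.4% to 8.1%), and the fall in power from 79% to between 46% and 64%. A loss of power is probable, but its size is not established. The evidence does not support a claim of type I error inflation or of a post hoc choice.

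This should be corrected before the analysis. It does not invalidate the design.

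**What to change.** Replace the rule with wording to this effect: TFI and VAS are analysed on their original scale whatever their distribution. Residuals from the mixed model are inspected. If they are clearly non-normal, the group difference is reported on the same scale with a bootstrap or robust-variance confidence interval.

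Do not simply delete the provision, because other secondary outcomes would then have none. Keep a log transformation for strictly positive secondary measures named in advance (matched tinnitus frequency is a candidate), and state the scale for the ERP measures. A log analysis of TFI can be kept as a sensitivity analysis, with the handling of zeros stated.

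The cost is a few sentences and a little more analysis work, with no new data. There is some loss of efficiency if residuals prove strongly skewed. With 65 to 83 patients per arm (166/2 = 83), a mean difference tolerates moderate non-normality.

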## Methods/design

There will be three test moments during the trial: before the start of therapy (T0), after the treatment sessions (T1) and 3 months after the last therapy session (T2). The primary and secondary outcome measurements will be assessed at every test moment. The difference between bimodal therapy 1 (TRT + CBT) and bimodal therapy 2 (TRT + EMDR) will be assessed. The experimental intervention, namely TRT + EMDR, will be compared to the active control group, namely TRT + CBT, as shown in the Consolidated Standards of Reporting Trials (CONSORT) flow diagram in Fig. 1. The Standard Protocol Items: Recommendations for Interventional Trials (SPIRIT) Checklist was utilized as guideline for this study (Additional file 1).

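### The fixed effects listed for the mixed model yield a group effect averaged over T0, T1 and T2, not the between-arm difference in TFI decrease

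*Protocol article*

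**What the plan says.** The Statistical methods section of the protocol article plans linear mixed models, "accounting for the non-independence of observations within the same individual by including random effect terms into the model". On the response side, "The outcome measurements will be entered as dependent variables". On the explanatory side, "Intervention group (TRT + CBT versus TRT + EMDR) and test moment (T0, T1, T2) are entered as fixed effects". The paragraph closes with the test to be made: "The effect of bimodal therapy 1 (TRT + CBT) versus bimodal therapy 2 (TRT + EMDR) will be verified". T0 is a level of the time factor, so the pre-treatment score is part of the outcome vector and not a covariate.

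Two other places define what is to be compared. The section on the Tinnitus Functional Index gives the primary focus as "A decrease in the score on the TFI in the TRT-CBT treatment group versus a decrease in the TFI score in the TRT- EMDR-treatment group". The Sample size calculation works with 0.7 SD between groups, "simplifying the calculation by considering the change in outcome between the first and the last point". Both describe change from baseline.

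**The concern.** Comparing a decrease in one arm with a decrease in the other is a group-by-time contrast. A model with a group term and a time term, and no product of the two, has no parameter for it. It forces the arm difference to be the same at T0, T1 and T2, although nobody has been treated at T0.

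If the model is run as listed, three things follow. The reported group effect understates the treatment difference. It is not the quantity used to size the trial. Part of any chance T0 difference is carried into it. The model also cannot address whether one therapy brings relief sooner, which the article's discussion poses as part of the main objective, because a constant arm difference has no timing in it.

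**Working it through.** **Plan's own figure.** For a difference of 0.7 SD of change, two-sided α = 0.05 and 80% power, the normal approximation gives 2(1.96 + 0.84)²/0.7² ≈ 32.0, so 33 per arm; the exact t calculation gives 34. The stated 65 is therefore not reproduced. That is a separate matter, but it sets the benchmark here: 65 per arm at 0.7 SD of change gives 97.7% power for a change-score comparison.

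**Inputs.** From the article: three visits, 65 per arm, 0.7 SD of change, two-sided 5%. Assumed: complete data, unit SD at each visit, equal correlation r between visits, and no expected arm difference at T0. The article does not give r, so a range is shown.

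**What the group coefficient estimates.** With arm differences d0, d1, d2 at the three visits, the coefficient has expectation (d0 + d1 + d2)/3. Put d0 = 0 and let D be the true difference in change:
- effect equal at T1 and T2: (0 + D + D)/3 = 2D/3;
- effect at T2 only: (0 + 0 + D)/3 = D/3.

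This does not depend on r. A 100-run simulation (r = 0.5, D = −0.70, effect at T1 and T2) gave a mean group estimate of −0.44 from the main-effects model, where the algebra gives −0.47. With the interaction the T2-versus-T0 estimate averaged −0.74. With so few runs this checks the direction, not the decimals.

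**Power.** The SD of change is √(2(1−r)), so D = 0.7√(2(1−r)). The SD of a patient's three-visit mean is √((1+2r)/3). The standardised effect for the group test is (2D/3)/√((1+2r)/3), or half of that if the effect is at T2 only. For r = 0.5: D = 0.700, SD of the mean = 0.816, so 0.467/0.816 = 0.57. Exact-t power at 65 per arm:

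| r | D | Group test, effect at T1 and T2 | Group test, effect at T2 only | Change contrast |
|---|---|---|---|---|
| 0.3 | 0.828 | 99% | 57% | 98% |
| 0.5 | 0.700 | 90% | 37% | 98% |
| 0.6 | 0.626 | 79% | 28% | 98% |
| 0.7 | 0.542 | 63% | 21% | 98% |
| 0.8 | 0.443 | 43% | 15% | 98% |

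**Chance baseline difference.** A T0 difference b has expected value rb at T1 and at T2, so it contributes (b + rb + rb)/3 = b(1+2r)/3 to the group estimate. That is 53% of b at r = 0.3, 67% at 0.5, 80% at 0.7 and 87% at 0.8. The unadjusted change contrast is not immune either: it carries rb − b = −(1−r)b. Conditioning on T0 removes both.

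**The case against.** The strongest reply is that silence is being read as exclusion. This is one paragraph in a journal article. Naming two factors need not list every model term, and contrasts are often left to a fuller plan. The outcome and sample size sections suggest that a differential change was intended. This stands in part. A reader might infer that the plan rules out an interaction, and the text does not say so. The point is nevertheless more than missing detail, because the article does fix the fixed effects, and the terms it fixes do not answer its own primary question.

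A reader might also infer that the trial is underpowered. The article does not support that. At its own effect size the group test keeps 90% power or more for r up to 0.5 when the effect is present at both post-treatment visits. At r = 0.3 it slightly exceeds the change contrast.

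Finally, a reader might infer that baseline imbalance makes false positives likely, particularly as the allocation sequence is tied to referral date. Under proper randomisation, chance imbalance is covered by the standard error and the test holds its 5% level. Nothing in the article links referral date to baseline TFI. What remains is that an imbalance that does occur feeds into the estimate when T0 data could have been used to remove it.

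**Conclusion.** The concern holds as a mismatch within the article. The fixed effects as listed give a group parameter that is neither the difference in TFI decrease nor the T0-to-last change used for sample size. The dilution to 2/3 or 1/3 of the true difference holds at any correlation, given complete data, no expected T0 difference, and a listed set of terms that is the whole model. The power consequence is conditional: none at low r with an effect at both visits, substantial from r of about 0.6 upward, and large at every r examined if the effect appears only at T2. The algebra is firm. Whether the investigators meant to omit the interaction cannot be settled from the article.

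**What to change.** State that the model includes group × test moment and that the treatment effect is read from that term. Name the T0-to-T2 contrast as primary, to match the sample size basis, and report the T1 contrast as well for the question of earlier relief. That alone recovers the stated quantity.

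Preferably go one step further. Model TFI at T1 and T2 as outcomes with group, test moment, group × test moment and T0 TFI as a covariate, and take the adjusted group difference at T2 as primary. Alternatively, keep T0 as an outcome with the two arms' T0 means constrained to be equal. T0 should not be both an outcome row and a covariate. The gain is precision: under equal correlation the variance of the T2 comparison falls from (2/n)·2(1−r) to (2/n)(1−r²), a ratio of (1+r)/2, or 0.75 at r = 0.5. Use the same form for the continuous secondary outcomes.

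The cost is one or two sentences and no new data, since the outcomes are already assessed at every test moment. The article reports recruitment still under way and defers unblinding to the end of the study, so the wording can be settled before results by arm are seen.
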